### Secondary outcome measures

#### **
*Periprosthetic joint infection markers*
**

Early diagnosis of PJI is challenging; at the present time, diagnosis of PJI remains dependent on clinical judgment and reliance on standard clinical tests including serologic tests, analysis of aspirated joint fluid, and interpretation of intraoperative tissue and fluid test results. During 3-month and 6-month follow-up, the CRP, ESR, synovial fluid culture, white blood cell (WBC) count and polymorphonuclear cell percentage (%PMN) will be measured.

### Safety

The presence of side effects during the postoperative period will be recorded, including nausea, vomiting, constipation and other adverse events.

### Sample size

Calculation of sample size was based on two previous studies [20,25]. We assumed that postoperative pain during the 24- to 48-hour period will reach peak value and need effective pain control. Mean VAS scores over 24 to 48 hours for the two modes of analgesia were extracted. Group sample sizes of 93 for each group will achieve 80% power to detect a difference of 1.0 between the null hypothesis that both group means are 2.8 and the alternative hypothesis that the mean of group E is 1.8, with estimated group standard deviations of 3.1 and 1.4 and with a significance level (alpha) of 0.05 using a two-sided *t*-test. We plan to enroll a total of 214 participants with 107 in each group, allowing for a 15% withdrawal rate.

### Data analysis

The statistical analysis will be performed using SPSS (Version 17.0) software (SPSS Inc., Shanghai, China). Normally distributed continuous variables will be compared using Student’s *t*-test. VAS and A-ROM will be analyzed with repeated measures for general linear models and multivariate analysis of variance. Data will be expressed as means (standard deviation), absolute numbers, and frequencies, when appropriate. *P* < 0.05 will be considered statistically significant for all comparisons.

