### Interventions

All recruited patients will receive combined spinal and epidural anesthesia at the L3-4 level. For all the patients, cefamandole (2 g) will be administered intravenously 30 minutes before and after surgery. Low-molecular-weight heparin (4,500 U) for thromboprophylaxis will be administered subcutaneously 8 hours postoperatively and then once daily until week 2. In group E, the heparin administration will be delayed until epidural catheter withdrawal on postoperative day (POD) 2. A standardized intraoperative regimen for fluid administration will be applied which consists of 0.9% saline at 5 ml/kg per hour and colloid (Voluven; Fresenius Kabi, Bad Homburg, Germany) at 7.5 ml/kg per hour.

For multi-model pain management, preoperative oral doses of 400 mg celecoxib daily will be administered from day 2 before surgery. Postoperatively, all patients will receive 40 mg of parecoxib sodium twice daily intravenously until POD 3, followed by oral doses of 200 mg celecoxib every 12 hours until discharge. Tramadol hydrochloride injection will be applied for rescue analgesia.

The same surgeon will perform all operations. A Gemini MK II prosthesis (LINK, Hamburg, Germany) will be inserted via a standard medial parapatellar approach in all patients.

#### **
*Cocktail anesthetic preparation*
**

Cocktail anesthetic will be prepared for continuous intra-articular infusion, containing 150 mg ropivacaine (20 ml), 3 mg morphine sulfate (0.3 ml), 30 mg ketorolac tromethamine (1 ml), 0.5 μg 1:1000 epinephrine (0.5 ml), mixed with normal saline into a total volume of 150 ml.

#### **
*Continuous intra-articular infusion anesthesia group (group C)*
**

In group C, 50 ml of cocktail anesthetic will be applied via periarticular infiltration before insertion of the prosthesis. A multi-holed catheter will be placed into the lateral parapatellar gutter. The remaining 100 ml will be used as continuous intra-articular infusion with a patient-controlled analgesic (PCA) pump (Fornia, Zhuhai, China) at a speed of 2 ml/hour. After the wound is sutured, the catheter will be connected to the PCA pump which is activated after surgery and removed 48 hours later. The PCA pump will be set to deliver a 0.5-ml dose with a 15-minute lockout interval.

#### **
*Epidural infusion anesthesia group (group E)*
**

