In group E, the epidural catheter position will be checked with a test dose of 3 ml lidocaine-adrenalin (20 mg/ml and 5 μg/ml), followed by a bolus of 7 ml ropivacaine (2 mg/ml). A PCA pump containing 200 mg of ropivacaine (2 mg/ml) and 4 mg of morphine (0.04 mg/ml) will be connected with a flow rate of 2 ml/hour for 48 hours postoperatively. The PCA will be programmed to provide a 0.5-ml dose with a lockout interval of 15 minutes.

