### Primary outcome measures

#### **
*Visual analogue scale*
**

The visual analog scale (VAS) has been used extensively for rating pain intensity in previous studies [22-24]. Postoperative pain at 2, 6, 10, 18, 26, 34, 42, 50, 58, 64, and 72 hours after surgery will be recorded using a VAS. The VAS consists of a 10-cm horizontal line with 1-cm vertical lines at each end labeled "no pain" (left side) and "worst possible pain" (right side).

#### **
*Rescue analgesia frequency and consumption*
**

Usually the need for supplementary treatment with systemic opioids is a reliable indicator when concerned about postoperative pain control. In previous studies, it has been argued that the use of strong or long-term rescue analgesia in both treatment groups may have reduced pain too much and “washed out” any differences between the two treatments. In this study, we use tramadol hydrochloride injection, which is a mid-intensity analgesic that will facilitate observing the differences in pain control between groups. The frequency and total consumption during the first 3 postoperative days will be recorded.

#### **
*Active range of motion*
**

Traditionally, range of motion has been used as an outcome measure after TKA to evaluate functional recovery and the success of the type of analgesia used [4-6,12]. However, we think active range of motion (A-ROM) represents a more realistic criterion for assessment of functioning and analgesia efficiency after TKA. A-ROM will be measured in the first 3 postoperative days and at the 3-month and 6-month follow-up.

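### The VAS test that was powered (24-48 h mean, two-sided t-test) is not among the VAS tests the analysis section names, so the stated 80% power attaches to none of them

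*Protocol article*

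**What the plan says.** **Sizing (Protocol article, Sample size).** The powered quantity is mean VAS over 24 to 48 hours: 2.8 in both groups under the null, 1.8 in group E under the alternative, with "estimated group standard deviations of 3.1 and 1.4", two-sided t-test, alpha 0.05, 93 per group for 80% power. Enrolment is 107 per group, "allowing for a 15% withdrawal rate".

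**Analysis (Data analysis).** "VAS and A-ROM will be analyzed with repeated measures for general linear models and multivariate analysis of variance". For other continuous outcomes: "Normally distributed continuous variables will be compared using Student’s" t-test. The section names no time window for VAS and does not say whether the group main effect, the group-by-time interaction or the multivariate test decides.

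**Readings (Primary outcome measures).** "Postoperative pain at 2, 6, 10, 18, 26, 34, 42, 50, 58, 64, and 72 hours after surgery will be recorded using a VAS". A-ROM is taken over the first three postoperative days and again at 3 and 6 months.

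**Infusions (Interventions).** In group C "the catheter will be connected to the PCA pump which is activated after surgery and removed 48 hours later". In group E the pump runs "with a flow rate of 2 ml/hour for 48 hours postoperatively". Both therefore end at 48 h.

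**The concern.** A power statement holds for one test of one quantity. Here that quantity is a three-reading mean inside the infusion period, while the named analysis takes in all 11 readings. Three consequences follow.

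- **Target.** The between-group test of a repeated-measures GLM compares averages over every reading, including the four after the infusions. If the treatments differ mainly during infusion, that average is smaller than the 1.0 assumed. The same test on A-ROM would mix early recovery with function at 3 and 6 months.
- **Missing readings.** Repeated-measures GLM and MANOVA need a full row per patient. One missed reading out of 11 normally removes the patient. The withdrawal allowance covers lost patients, not scattered gaps, and bias arises if gaps relate to pain or complications.
- **Variance.** These methods and Student's t-test assume a common variance or covariance. The planned SDs imply a variance ratio of (3.1/1.4)² = 4.9.

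**Working it through.** **1. Reproduce the stated figure.** SE = √(3.1²/93 + 1.4²/93) = √(11.57/93) = 0.353, so the noncentrality is 1.0/0.353 = 2.84. The unequal-variance noncentral t gives 80.3% power. The plan's 93 per group is sound for the test it describes. After 15% withdrawal, 107 × 0.85 ≈ 91 per group remain, with power 79.5%.

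**2. Count the readings.** Seven fall at 2-42 h, three of them (26, 34, 42 h) within 24-48 h. Four (50, 58, 64, 72 h) fall after the infusions.

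**3. Power of the 11-reading group main effect at 93 per group.** If the 1.0 difference holds through 42 h and is zero afterwards, the average difference is 7/11 = 0.64. The SDs 3.1 and 1.4 are taken as those of a three-reading mean. Under compound symmetry with within-patient correlation ρ (assumed; the document gives none), they are multiplied by √[(1+10ρ)/11] / √[(1+2ρ)/3].

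| ρ | SD factor | Difference ends at 48 h (0.64) | Difference persists to 72 h (1.0) |
|---|---|---|---|
| 0.3 | 0.826 | 58% | 93% |
| 0.5 | 0.905 | 51% | 88% |
| 0.7 | 0.953 | 47% | 84% |
| 1.0 | 1.000 | 43% | 80% |

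If half the difference persists, the average is 9/11 = 0.82, and power is 63% with the SDs unchanged. If 3.1 and 1.4 are read as single-reading SDs instead, the case in which the difference ends at 48 h gives 47-84% for ρ from 0.9 to 0.3.

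**4. Other tests the named methods produce.** These were simulated at 93 per group with the difference confined to 2-42 h. With the SDs read as single-reading values and ρ = 0.5, power is 68% for the main effect and over 99% for both MANOVA and group-by-time. With a constant difference the order reverses: 97% main effect, 71% MANOVA, 6% group-by-time.

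**5. Complete rows.** The document gives no missing-reading rate. Assume a share m of readings is missing independently, so the complete share is (1−m)^11. Power is for a 1.0 difference with the SDs unchanged.

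| m | Complete | From 107 per group | From 91 per group |
|---|---|---|---|
| 1% | 90% | 81% | 75% |
| 2% | 80% | 77% | 70% |
| 3% | 72% | 72% | 65% |

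**6. Common variance.** At 93/93 the pooled and Welch tests have the same t statistic. Simulated power is 80.8% and 80.6%, type I error 5.0% and 4.9%. With uneven completers, and SD 3.1 assigned to group C from the order in which the values are given, pooled type I error is about 6.8% at 82 C versus 100 E and about 3.7% at 100 C versus 82 E. Welch stays near 5% in both.

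**The case against.** Four points can be made on the other side.

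- **Unequal variances cost no power here.** Correct. At 1:1 allocation a reader might infer that the equal-variance assumption itself erodes the stated power, but step 6 shows it does not. Harm needs uneven completers, and the document predicts none. A modest split of 88 versus 94 gives about 5.5%. Reaching 7.6% takes 80 versus 107, which is 25% loss in the high-SD arm and none in the other.
- **Complete-case analysis is nowhere stated.** Also correct. It is how the named procedures normally behave, and a missing-data rule may stand in a document not shown. The 15% allowance already covers whole-patient loss. The figures in step 5 rest on assumed rates and on independence.
- **Dilution is conditional.** It requires that the difference fades after 48 h and that the group main effect decides. The document settles neither, and step 4 shows that other tests from the same methods need not lose power.
- **Readings to 72 h are legitimate.** Pain to 72 h is a prespecified primary outcome, and the Background says pain lasts that long and raises rebound pain. Collecting these readings is not an error. Nor does the document say that days 1-3 and months 3 and 6 of A-ROM are averaged, since a time factor can separate them.

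All four limit the size of the point. None supplies the missing link: the tests respond in opposite directions to the same pattern of effect, and nothing says which one carries the 80%.

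**Conclusion.** The mismatch stands. The power calculation is for the 24-48 h mean by t-test, the named VAS analysis is repeated-measures GLM/MANOVA over 11 readings, and the 80% belongs to no VAS test that the Data analysis section names.

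Its size depends on unstated choices. For the 11-reading main effect at 93 per group, power is about 43-58% if the 1.0 difference ends with the infusions and 80-93% if it persists, for correlations from 1.0 to 0.3 and the SDs read as those of a 24-48 h mean. Under 1-3% of readings missing independently, complete-row analysis gives about 81-72% from 107 per group, or 75-65% from 91. The common-variance assumption is a type I error issue under uneven completers only.

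A reader might go further and conclude that the plan as written loses its stated power. The document does not support that. The loss depends on the effect fading, on the main effect being decisive, or on missed readings at a rate nobody has given. This is a change that should be made because it is cheap and removes the ambiguity. It does not show that the trial is underpowered.

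**What to change.** - Name the group contrast over 26, 34 and 42 h as the primary VAS test, so that the test matches the sample size calculation.
- Estimate it in a linear mixed model using all observed readings, with arm-specific variances. Scattered missing readings then do not remove the patient.
- Report the 50-72 h readings as a separate contrast, which also addresses rebound pain directly.
- For A-ROM, give separate contrasts for days 1-3 and for months 3 and 6.
- For single comparisons, replace Student's t-test with Welch's.

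The cost is revised analysis wording and slightly more programming. The planned software ("The statistical analysis will be performed using SPSS (Version 17.0) software") offers linear mixed models. No extra data or patients are needed.

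### Three primary outcomes are each tested at 0.05 with no rule for which decides, while the sample size spends a single 0.05 on a VAS summary that is never named as the deciding contrast

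*Protocol article*

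**What the plan says.** Under Primary outcome measures the protocol article gives three headings.

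- VAS: "Postoperative pain at 2, 6, 10, 18, 26, 34, 42, 50, 58, 64, and 72 hours after surgery will be recorded using a VAS". That is 11 readings.
- Rescue analgesia: "The frequency and total consumption during the first 3 postoperative days will be recorded". That is two measures.
- A-ROM: "A-ROM will be measured in the first 3 postoperative days and at the 3-month and 6-month follow-up".

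The Data analysis section assigns VAS and A-ROM to repeated-measures general linear models and multivariate analysis of variance. For significance it says that P below "0.05 will be considered statistically significant for all comparisons".

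The Sample size section rests on a single contrast: "Mean VAS scores over 24 to 48 hours for the two modes of analgesia were extracted". The claim is "Group sample sizes of 93 for each group will achieve 80% power to detect a difference of 1.0", under a null that "both group means are 2.8 and the alternative hypothesis that the mean of group E is 1.8", "with a significance level (alpha) of 0.05 using a two-sided" t-test. The standard deviations are 3.1 and 1.4.

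The Discussion calls reducing discomfort the primary goal and lowering narcotic cost a secondary one. It then gives a primary purpose that covers pain, narcotic need and function together.

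**The concern.** Three outcomes share primary status, and each is allowed the full 0.05. The sample size spends that same 0.05 once, on a 24 to 48 hour VAS mean. That mean is not defined as an outcome and is not named as a contrast of the planned model. A reader of the final report could not tell which result the alpha and power were attached to.

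Two things are at stake. First, the chance that at least one primary result is significant by luck exceeds the 5% used in the sizing. Second, the outcomes may disagree. The sizing alternative has group E with the lower pain score (1.8 against 2.8), while the Discussion sets out to show benefit from the group C technique. Pain favouring one arm and A-ROM the other is a plausible result, and the stated rule would make both of them significant primary findings.

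**Working it through.** **Step 1. Reproduce the plan's figure.** Inputs from Sample size: difference 1.0, SDs 3.1 and 1.4, two-sided alpha 0.05, power 80%.

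- Root-mean-square SD = sqrt((3.1² + 1.4²)/2) = sqrt(5.785) = 2.405.
- Normal approximation: n = 2 × (1.960 + 0.842)² × 5.785 / 1.0² ≈ 90.8, so 91 per group.
- Unequal-variance t-test (Welch degrees of freedom, noncentral t): 92 per group gives 79.9% and 93 gives 80.3%.

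The stated 93 is reproduced, for one test at 0.05.

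**Step 2. Count the primary tests.**

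- Following the stated models, with one overall group test for VAS, one for A-ROM and two for rescue analgesia: 4 tests.
- Treating rescue analgesia as one test: 3.
- Testing every time point separately, and assuming one A-ROM reading on each of the 3 days plus months 3 and 6: 11 + 2 + 5 = 18.

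**Step 3. Chance of at least one false positive, no true difference on any outcome.** If independent, this is 1 − 0.95^k. The correlated figures come from a simulation of two-sided z-tests (400,000 draws). The documents give no correlations, so they are assumed: 0.3 to 0.9 within an outcome family and 0.1 to 0.5 between families.

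| Tests | Independent | Assumed positive correlation |
|---|---|---|
| 3 | 1 − 0.95³ = 14.3% | about 12.5% to 14% |
| 4 | 1 − 0.95⁴ = 18.5% | about 14% to 18% |
| 18 | 1 − 0.95¹⁸ = 60.3% | about 24% to 55% |

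Every row is above 5%.

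**Step 4. Compare the remedies.** Power is for the VAS contrast of Step 1 at 93 per group (Welch). The n needed for 80% power uses the normal approximation, before withdrawals.

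| Rule | Alpha for VAS | Power at 93 | n per group needed |
|---|---|---|---|
| One primary | 0.05 | 80.3% | 93 as planned |
| Bonferroni over 3 | 0.05/3 = 0.0167 | 65.9% | 122 |
| Bonferroni over 4 | 0.05/4 = 0.0125 | 61.9% | 130 |

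**Step 5. Locate the sizing window.** Of the 11 VAS times, those between 24 and 48 hours are 26, 34 and 42. The sized contrast can therefore be built from data already planned.

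**The case against.** **The plan uses overall models, not point-wise tests.** This stands. A reader might infer 18 comparisons and a 60% error rate from the list of measurement times. That list says only when data are recorded, and the Data analysis section assigns VAS and A-ROM to repeated-measures and multivariate models. The 60% would apply only if each time point were tested separately and the tests were independent. Three or four tests is the fair count. Rescue frequency and total consumption describe the same tramadol use, so they are probably strongly correlated, which pulls the figure towards the three-test row.

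**The trial is sized on a declared primary.** This largely stands. A reader might infer that the sizing endpoint lies outside the primary outcomes. It does not: it is a summary of VAS, the first outcome listed. The narrower complaint is that this summary is not named as the one that decides.

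**The Discussion supplies a hierarchy.** In part. Calling reduced discomfort the primary goal, together with sizing on VAS, points to pain as the lead outcome. The same paragraph then puts pain, narcotic need and function under one primary purpose, so the question stays open.

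**Testing order belongs in a SAP, and no success rule is stated.** Silence on testing order would indeed be no finding in a condensed article. But the list of three primaries and the 0.05 threshold for every comparison are stated, and a later document could repair them only by departing from one or the other. That any single significant result would be claimed as success is an inference: the text does not say so, it only leaves it open. If all primaries had to succeed there would be no inflation, but no such rule appears. Under it, overall power could not exceed that of the VAS test and would usually be lower.

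**Conclusion.** The concern holds in this limited form. The article fixes three primary outcomes and an unadjusted 0.05 for all comparisons, while its alpha and power describe one VAS contrast that it does not name as decisive. Under the models as stated, the chance of at least one false-positive primary is 18.5% with four independent tests, about 14% to 18% with assumed positive correlation, and about 12.5% to 14% with three correlated tests. That is roughly 2.5 to 3.7 times the nominal 5% (12.5/5 = 2.5; 18.5/5 = 3.7).

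These figures assume no true difference on any outcome, that a significant result on any one primary could be reported as a positive finding, and the correlations given above. The sample size arithmetic itself is sound for the single contrast. It matters because the trial's main conclusion depends on which result is taken as decisive.

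**What to change.** - In Primary outcome measures, name one primary endpoint: the group C minus group E difference in each patient's mean VAS over 24 to 48 hours (readings at 26, 34 and 42 hours), tested two-sided at 0.05. This matches the sizing and keeps 93 evaluable per group at 80.3% power, taking the sizing SDs to apply to this three-reading mean.
- Make rescue tramadol and A-ROM secondary, either tested in a fixed order or reported with 95% confidence intervals.
- Amend the sentence in Data analysis that applies 0.05 to every comparison, and name the 24 to 48 hour contrast there.
- Reconcile the Background, which places peak pain at 3 to 6 hours after surgery, with the Sample size section, which assumes the peak at 24 to 48 hours. Report the early VAS readings (2, 6, 10 and 18 hours) as a key secondary.

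The cost is a few lines of wording, with no change to data collection or treatment. There are two downsides: rescue use and A-ROM lose primary status, and the primary window leaves out the early period in which the Background expects the worst pain. Keeping all outcomes primary with a Bonferroni split would instead need about 122 (three tests) or 130 (four tests) evaluable patients per group for the VAS contrast.

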## Discussion

This study will provide clinical evidence on the efficacy of a continuous intra-articular infusion technique in reducing pain and improving postoperative function. In TKA, this remains a significant problem in the early postoperative period. Reduction of the patient's discomfort is the primary goal; reduction of the cost of narcotic use is a secondary goal. The epidural analgesia has been regarded as the gold standard in postoperative pain management, and it is associated with potential problems such as motor block, urinary retention and epidural bleeding (with anticoagulation therapy), and necessitates intensive observation of patients. The primary purpose of our study is to evaluate the efficacy of a continuous intra-articular infusion technique in relieving postoperative pain, reducing the need for postoperative narcotics, and improvement in postoperative function.

This study will be the first randomized controlled trial to investigate infection risk with a continuous intra-articular infusion technique after TKA. There has been concern about the risk of early PJI with periarticular multimodal drug injection and use of intra-articular catheters after TKA. Previous studies of local infiltration analgesia after unicompartmental knee arthroplasty or TKA have not found any increase in infection [7,15,20,26], but the evidence has been weak in most studies. At the present time, diagnosis of PJI remains dependent on clinical judgment and reliance on standard clinical tests including serologic tests and analysis of aspirated joint fluid. For this purpose, we will measure the ESR, CRP, synovial fluid cultures, WBC count, and %PMN at the 3-month and 6-month follow-up to identify early infections related to the surgical procedure.

